##### Emergency unblinding procedure

There are no likely situations that would mandate emergency unblinding. Complications of corticosteroids are very well known and would not warrant change in management if treatment allocation was known, even in an emergency care setting. The comparator (placebo, normal saline) does not contain an active substance and would not produce any significant AEs. Clinical deterioration in CIDP, possibly requiring unblinding, is slowly progressive and its management is not expected to take place in an emergency care setting. Management of clinical deterioration due to a concomitant condition (i.e. infection) is not changed by knowledge of treatment allocation. In the UK, in the event that a patient, or their treating physician, feels there is a an urgent need to find out whether the patient is receiving steroids or placebo, they should contact the Neurology Registrar on call at the respective participating institution to explain why treatment allocation needs to be revealed as a matter of urgency. Each patient will carry a card containing brief information about the trial, in order to allow any Neurology Registrar to understand what the query refers to. If the Neurology Registrar on call agrees there is a potential need to reveal treatment allocation, they will contact the centre PI. Emergency unblinding is the sole responsibility of the investigator. In order to ensure that this can be achieved without significant delay, UK centre PI’s can nominate sub-investigators via the delegation log, who can authorise emergency unblinding in the event that the PI cannot be reached within 30 min. If the centre PI authorises unblinding, there will be two different procedures to follow: one for UCLH and one for the other five UK participating sites. If the local PI authorises emergency unblinding, the Neurology Registrars on call at King’s College Hospitals London, The Walton Centre Liverpool, University Hospitals of Birmingham, Royal Victoria Infirmary Newcastle, or Queen Elizabeth University Hospital Glasgow will contact the pharmacy who will perform the unblinding by accessing accountability records. At UCLH, the clinical trials pharmacist will, upon receiving treatment allocation, print this information and put it in a sealed envelope with a signature and a patient label across the seal. These envelopes will be stored in a locked drawer in the office of the local PI. In the event that emergency unblinding is authorised at UCLH, the Neurology Registrar on call will contact the security officer who will assist the Neurology on call doctor in accessing the PI’s office for access to the relevant letter.

### Data collection and management

#### Plans for assessment and collection of outcomes {18a}

Outcomes will be assessed by the local investigator, or delegated (and trained) person, at follow-up visits as listed in Table 1. Table 2 lists the consultation by telephone. Questionnaires are sent to patients before telephone consultations take place. A time window of 3 days is accepted for all study procedures. A time window of 2 and 4 weeks is allowed for the week 52 and week 104 visits, respectively. HbA1c is assessed as part of standard care at baseline, 24 weeks and 52 weeks. If HbA1c has been assessed in the work up leading to the diagnosis, up to 3 months prior to enrolment, this measurement is allowed as baseline value.

**Table 2 Tab2:** Consultation by phone

	Consultation by phone (in weeks)
	3
**I-RODS**	X
**INCAT-DS**	X
**AEs**	X

*Abbreviations: I-RODS* inflammatory Rasch Disability Scale, *INCAT-DS* Inflammatory Neuropathy Cause and Treatment Disability Scale, *AE* adverse event

#### Plans to promote participant retention and complete follow-up {18b}

Patients who reach a preliminary endpoint or drop out of the study for whatever reason will be treated at physician’s discretion and will complete follow-up visits according to protocol. If patients are unable to complete follow-up, data obtained up until that point will be stored in eCRF and used in the analysis if appropriate. Additional visits are considered standard care and can be scheduled at the discretion of treating physician. There will be no replacement of individual patients after withdrawal.

#### Data management {19}

Source documents for each patient will be kept at the patient’s study site until the last follow-up visit of the last patient included. Records will include date of informed consent, visit dates, medical history, neurological examinations and study parameters, administration of other medication and (S)AEs. Data are recorded on a working document after which treating physician or research nurse will enter data in the eCRF. Patient questionnaires are completed on paper or electronically (and uploaded directly in database). After the end of study, individual patient data (pseudonymised source documents) are transferred and stored at the Trial office of the Department of Neurology, Amsterdam UMC, location AMC, Amsterdam, the Netherlands. After the end of the study, all essential forms pertaining to the conduct of the study will be archived by the investigator for a period of 15 years in accordance with the SOP of the Amsterdam UMC, location AMC. The coordinating PI and study sponsor are the only ones who have access to this information. All patient data are stored in a way that the privacy of participants is respected. Data validation procedures (such as reason for change logs, value and range checks, prompts and warnings if data are entered incorrectly) are built into the database to promote data quality. An audit trail is in place. Both a monitoring plan and data management plan are in place to promote data quality.

#### Confidentiality {27}

Data is collected pseudonymised using a PIN that will consist of the study site number and consecutive patient number. At each study site, there will be a PIN code list (identification log). Only the local investigators will have access to the PIN of patients treated at the study site. Study team, the safety committee supervising the study, a monitor supervising the conduct of the study and the Healthcare Inspectorate will have access to the eCRF and source file. The collection of data for medical research in the Netherlands is subject to the General Data Protection Regulation (GDPR), which replaced the Personal Data Protection Act (Wbp) in 2018, and in particular to the Medical Treatment Contracts Act. In the UK this is subject to the Data Protection Act (DPA) 2018 and the GDPR. Patient contact details (address and telephone number) will be provided to the home-care nurses, after consent by participants, by local investigators to enable distribution of study treatment and administration.

#### Plans for collection, laboratory evaluation and storage of biological specimens for genetic or molecular analysis in this trial/future use {33}

No biological specimens will be collected during this trial.

### Statistical methods

#### Statistical methods for primary and secondary outcomes {20a}

Baseline assessments, outcome and safety parameters will be summarised using simple descriptive statistics. Continuous, normally distributed variables will be expressed as means and standard deviations; continuous, non-normally distributed and ordinal variables as medians (25th–75th percentiles); and categorical variables as counts and percentages. Normality of data will be explored by a Normal Q-Q Plot and tested by the Shapiro-Wilk test. Statistical uncertainties will be quantified with two-sided 95% confidence intervals. All analyses will be based on the intention-to-treat principle, whereas the primary outcome (the number of patients in remission) and three secondary outcomes (time to improvement on disability, number of patients with improvement on disability ≥ MCID, and number of (S)AEs) will be additionally analysed on per-protocol basis. A two-sided *p* value < 0.05 will be considered statistically significant. We will not correct for multiple testing. Data analyses will be performed blinded for the allocated study intervention.

##### Primary outcome

The between-group difference in number of patients in remission (52 weeks after start of treatment) will be analysed using the chi-square test. Additionally, the primary outcome will be analysed using logistic regression, including the stratification variables (country, previous treatment) into the model. Effect size will be expressed as an adjusted odds ratio.

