### Sample size {14}

There are no robust figures on the long-term remission rates in patients treated with IVIg only. In a previous trial, remission during a 6-month period was seen in about half of IVIg responders, compared to 100% in IVMP responders [9]. However, a significant proportion of patients were not treatment naïve but known responders to IVIg. Furthermore, follow-up was shorter than the follow-up period in this study. We assume that the remission rate after IVIg is approximately 35% during an 8-month follow-up period. Treatment-naïve CIDP patients treated with dexamethasone had a long-term remission rate of 56% using a more stringent definition of improvement compared to this study [5, 8]. Our limited prospective pilot data of the OPTIC protocol suggest similar remission rates (59%) [10]. We assume remission rates of 35% in the IVIg/placebo group, and 65% in the IVIg/IVMP. A 30% difference in remission rate is large but warranted as IVMP may lead to various AEs in patients and because there is the alternative of continuing maintenance IVIg treatment. A two-group chi-square test with a 0.05 two-sided significance level will have 80% power to detect the difference between a control group proportion (IVIg/placebo) of 0.35 and a treatment group proportion (IVIg/IVMP) of 0.65 (odds ratio of 3.45) when the sample size in each group is 43 (86 patients in total). Anticipating on a 10% attrition rate due to AEs, we will include 48 (43/0.90) patients in each group (96 patients in total).

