### Assignment of interventions: allocation

#### Sequence generation {16a}

After signing the IC form, patients are randomised to either IVIg + IVMP or IVIg + placebo. Randomisation is performed using the functionality of Castor EDC. Randomisation is stratified per country (NL/UK) and previously administered treatment (treatment naïve versus previously treatment, inclusion group 2) with random permuted blocks of sizes 2 or 4 within the strata.

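### The main test of remission ignores the randomisation strata, while the only named effect size comes from a second, stratified model; one stratified analysis should decide

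*Protocol article*

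**What the plan says.** **Design.** Under Sequence generation {16a}, allocation is stratified by country and previous treatment, "with random permuted blocks of sizes 2 or 4 within the strata".

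**Analysis.** The Primary outcome paragraph of the statistical methods first states: "The between-group difference in number of patients in remission (52 weeks after start of treatment) will be analysed using the chi-square test". It continues: "Additionally, the primary outcome will be analysed using logistic regression, including the stratification variables (country, previous treatment) into the model". The effect size is then given as an adjusted odds ratio, and no other effect measure is named there. The general paragraph under {20a} sets two-sided p < 0.05 without multiplicity correction, and two-sided 95% confidence intervals.

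**Sizing.** Sample size {14} uses the unadjusted test: "A two-group chi-square test with a 0.05 two-sided significance level will have 80% power to detect the difference". The planning rates are stated as "We assume remission rates of 35% in the IVIg/placebo group, and 65% in the IVIg/IVMP". The clinical argument is on the absolute scale: "A 30% difference in remission rate is large but warranted", given the adverse events of methylprednisolone and the alternative of continuing immunoglobulin.

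**The concern.** Blocking within strata forces the arms to be nearly balanced on country and previous treatment. Differences in remission between strata then add almost nothing to the true variability of the treatment contrast. The crude chi-square still counts them as noise. If the strata are prognostic, its p value is on average too large and it uses less information than the design provides.

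There are two further mismatches:
- The test that comes first and the estimate that will be reported belong to different models. Near p = 0.05 the chi-square and the adjusted confidence interval can disagree, and no sentence says which prevails.
- The design is argued on a 30-point difference, but the named effect size is a conditional odds ratio. When the strata are prognostic, that quantity differs from the marginal odds ratio used in planning.

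At stake is some precision in a small trial of a rare disease, and clarity about which result is the trial's answer.

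**Working it through.** **1. The plan's own figures.** Inputs from Sample size {14}: rates 0.35 and 0.65, two-sided 5%, 80% power.

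- Pooled chi-square formula: n = [1.96·√(2·0.5·0.5) + 0.8416·√(0.35·0.65 + 0.65·0.35)]² / 0.30² = (1.3859 + 0.5677)² / 0.09 = 42.4, so 43 per group.
- Power at 43 per group: 80.6% by formula, 79.6% by exact enumeration.
- Odds ratio: (0.65/0.35)/(0.35/0.65) = 3.45.
- Attrition: 43/0.90 = 47.8, so 48 per group. If all 96 contribute, formula power is 84.8%.

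Everything stated reproduces.

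**2. Effect of ignoring the strata (large-sample).** The 2:1 ratio of Netherlands to UK patients is from Study setting {9}. Two inputs are assumptions, because the documents do not give them: a 70% treatment-naïve share, and an odds ratio for remission of 1 to 4 per stratification factor (the same for both). Overall rates are held at 35% and 65%, with 43 per group.

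- True size of the chi-square: 2·[1 − Φ(1.96/√(1 − R))], where R is the share of outcome variance lying between strata (at 50% overall remission).
- Power of the chi-square: Φ[(0.30 − 1.96·SE₀)/SE₁], where SE₀ = √(2·0.25/43) = 0.1078 and SE₁ = √(Σw[p_c(1 − p_c) + p_t(1 − p_t)]/43). Here w are the stratum shares, and p_c and p_t the stratum rates in the two arms.
- Power of the stratified test: the same, with SE₀ replaced by √(2·V/43), where V = Σw·p̄(1 − p̄) and p̄ is the stratum rate averaged over arms.

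Example with odds ratio 3 per factor:
- Stratum shares are 0.467, 0.200, 0.233 and 0.100. At 50% overall, stratum rates are 0.336, 0.603, 0.603 and 0.820.
- R = 0.1095, 1.96/√0.8905 = 2.077, so the true size is 3.8%.
- SE₁ = √(0.4091/43) = 0.0975. Chi-square: Φ(0.909) = 81.8%.
- V = 0.2273, √(2·0.2273/43) = 0.1028. Stratified: Φ(1.010) = 84.4%.

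| Odds ratio per factor | True size, chi-square | Power, chi-square | Power, stratified | Gap (points) |
|---|---|---|---|---|
| 1 | 5.00% | 80.56% | 80.56% | 0 |
| 1.5 | 4.80% | 80.75% | 81.15% | 0.4 |
| 2 | 4.45% | 81.10% | 82.22% | 1.1 |
| 3 | 3.78% | 81.83% | 84.37% | 2.5 |
| 4 | 3.24% | 82.48% | 86.14% | 3.7 |

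**3. Simulation** (blocks of 2 or 4 in four strata; 5,000 to 6,000 trials per setting at 86 patients, 70% naïve). Power, chi-square versus Cochran-Mantel-Haenszel:
- odds ratio 1: 79.1% versus 79.0%
- 1.5: 79.6% versus 80.5%
- 2: 79.5% versus 81.4%
- 3: 80.7% versus 84.2%
- 4: 82.8% versus 86.9%

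At odds ratio 3, size was 3.7% versus 4.8%. With 96 patients and 65% naïve assumed, the gain was 0 to 0.5 points at odds ratios of 1 to 2 and 2 points at 3. It reached about 4 points only when one factor had odds ratio 3 and the other 8.

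**4. Disagreement between the two p values** (simulation, 70% naïve, odds ratios 1 to 3 per factor). At 86 patients and 35% versus 65%, the chi-square and logistic p values fell on opposite sides of 0.05 in about 2 to 5% of trials. At 96 patients it was about 0 to 2%, rising to about 4% if the true rates were 35% versus 55%.

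**5. Scale of the estimate.** With marginal rates of 35% and 65% (odds ratio 3.45), the conditional odds ratio is about 3.5 to 4.0 for factor odds ratios of 1.5 to 3.

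**The case against.** The other side has real weight, and it rules out several stronger readings that a reader might infer.

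- **That the two p values are unranked.** The logistic model is introduced as an addition and the sample size rests on the chi-square, so the chi-square is primary by implication. What stands is that no sentence says so explicitly, and that the implied primary test does not produce the reported estimate.
- **That the trial is underpowered.** It is not. The stated 80% was computed for the chi-square and holds. Any loss is relative to a stratified test, and the departure in size is conservative, so there is no added false-positive risk.
- **That the chi-square certainly loses power.** It does so only if the strata predict remission. The documents give no figure for this, and with non-prognostic strata the loss is nil.
- **That the confidence interval is too wide.** The interval for the named effect size comes from the model that contains the strata. The complaint applies to the chi-square p value only.
- **That the result cannot be set against the 30-point target.** Categorical outcomes are to be summarised as counts and percentages, so the crude difference will be visible, and the sample size section also gives the target as an odds ratio of 3.45. What is missing is a difference, with its interval, named as an effect measure and consistent with the deciding analysis.

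One may also say that ranking the analyses is detail for a statistical analysis plan, which is not shown. But the article does not leave the matter open: it puts an unstratified test first and takes the effect size from another model.

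**Conclusion.** The mismatch between design, test and estimate is real but modest in size. Relative to a stratified test, the chi-square gives up nothing if the strata are not prognostic, about half a point to 2 points of power for odds ratios of 1.5 to 2 per factor, and about 2 to 4 points for odds ratios of 3 to 4. Its true size is then about 3 to 4% instead of 5%. Conflicting conclusions from the two models are uncommon, but they arise in borderline results, where a rule is needed. These figures rest on an assumed prognostic strength and an assumed naïve share; over naïve shares of 50 to 90% the large-sample gap stays between 0 and about 4 points. The sample size and planned power stand as written.

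**What to change.** Name one deciding primary analysis that uses the randomisation strata: either the Cochran-Mantel-Haenszel test or the logistic model already planned. Take the primary p value and estimate from it. Add a stratified or standardised risk difference with 95% confidence interval, so that the result can be read directly against the 30-point target, and keep the adjusted odds ratio alongside. Label the crude chi-square a sensitivity analysis.

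If the logistic model is chosen, state which test gives the p value. In the simulations at 86 patients with no treatment effect, the likelihood-ratio test rejected in 5.2 to 6.2% of trials, against 4.25 to 5.6% for Cochran-Mantel-Haenszel. Use the strata as they were applied at randomisation, and say where patients with a single prior immunoglobulin course belong: Sequence generation {16a} ties the previously treated stratum to inclusion group 2.

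The cost is wording only. Sample size, conduct and data collection do not change. The change must be made before the randomisation code is broken, which the plan places after database lock; the article reports 34 of 96 patients enrolled at the time of writing.

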## Trial design {8}

The OPTIC trial is an international, multicentre, randomised, double-blind, placebo-controlled, parallel group superiority trial with two treatment arms allocated in a 1:1 ratio.

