### Outcomes {12}

#### Primary outcome

The primary outcome is the number of patients in remission at 52 weeks after start of treatment. Remission is defined as sustained improvement without the need for further treatment. Improvement is defined as improvement by at least the minimal clinical important difference (MCID) on the inflammatory Rasch-Overall Disability Scale (I-RODS) and/or improvement of one or more points on the adjusted Inflammatory Neuropathy Cause and Treatment Disability Scale (INCAT-DS) at 18 weeks (end of treatment) compared to baseline. For the I-RODS, MCID is calculated using a statistical approach in which an increase of 1.96 SE is considered relevant improvement [12]. For the adjusted INCAT-DS, a decrease of 1 point or more is considered a relevant improvement [13, 14]. Changes in upper limb function from ‘0’ (normal) to ‘1’ (minor symptoms) or from ‘1’ to ‘0’ are not considered relevant deterioration or improvement [13]. Sustained is defined as no deterioration between 18 and 52 weeks, i.e. difference on the I-RODS of less than the MCID difference and/or less than one point on the adjusted INCAT-DS. Patients will be considered a treatment failure if they (1) received additional CIDP treatment during the 18-week intervention period, (2) do not improve at 18 weeks, (3) restart CIDP treatment for any reason between 18 and 52 weeks, or (4) do not show a sustained improvement at 52 weeks as defined above.

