##### Secondary outcomes

For all secondary outcomes, except care use and health care costs, between-group differences will be assessed at both 18 and 52 weeks after start of treatment, or earlier if a preliminary endpoint is reached. Between-group differences in time to MCID-based improvement on disability are analysed by plotting Kaplan-Meier curves and comparing them using the log-rank test. Between-group difference in the number of patients with MCID-based improvement on disability (I-RODS and/or INCAT-DS) will be analysed using the chi-square test. Differences between mean change scores from baseline to follow-up with regard to disability, grip strength, muscle strength, sensory impairment, fatigue and pain will be analysed using the two-group *t* test. HRQL follow-up data (derived from the EQ-5D-5L profiles) will be assessed by repeated measurement analysis, using a linear mixed model. Additionally, the 18- and 52-week follow-up scores of these continuous outcome parameters will be analysed using multivariable linear regression models with the follow-up scores as the dependent variables, and treatment groups, the baseline values and the stratification variables as the independent variables. The repeated data structure of the secondary outcomes (data of the complete 52-week follow-up) will also be analysed using linear mixed models with treatment group membership as a fixed-effect and an appropriate random-effect structure.

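### The model that gives the remission odds ratio adjusts for country and previous treatment but not for baseline I-RODS or INCAT-DS; the plan is valid, but precision is given up and chance imbalance stays in the estimate

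*Protocol article*

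**What the plan says.** All references are to the protocol article.

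- **Statistical methods, Primary outcome.** The group difference in remission is tested by chi-square. A further analysis is a "logistic regression, including the stratification variables (country, previous treatment) into the model", and the effect size is the adjusted odds ratio from that model. No other effect measure is named for remission.
- **Outcomes {12}, Primary outcome.** Improvement is judged at week 18 against baseline, on the I-RODS, the adjusted INCAT-DS, or both. One kind of INCAT-DS change is discounted: "Changes in upper limb function from ‘0’ (normal) to ‘1’ (minor symptoms) or from ‘1’ to ‘0’ are not considered relevant deterioration or improvement".
- **Table 1.** I-RODS and INCAT-DS are both scheduled at baseline.
- **Eligibility criteria {10}.** No minimum disability score is set.
- **Sequence generation {16a}.** The randomisation strata are country and previous treatment. Disability is not one of them.
- **Statistical methods, Secondary outcomes.** The 18- and 52-week continuous scores are modelled with "treatment groups, the baseline values and the stratification variables as the independent variables".
- **Methods for additional analyses {20b}.** None are planned, so no baseline-adjusted analysis of remission appears elsewhere.
- **Sample size {14}.** "A two-group chi-square test with a 0.05 two-sided significance level will have 80% power to detect the difference", with 35% and 65% in remission.

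**The concern.** Whether a patient can count as improved depends partly on where that patient starts. An INCAT-DS of 0, or of 1 from the arm item alone, leaves no countable improvement on that scale, and a patient near the top of the I-RODS has little room on the other. Baseline disability is therefore a natural candidate predictor of remission. It is not balanced by design, and it is already in the database. The plan adjusts for baseline when the two scales are analysed as continuous secondary scores, but not when they are combined into the primary outcome, and it gives no reason.

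Two things are at stake. If baseline disability is prognostic, an adjusted analysis has more power with the same 96 patients, in a rare disease where the article reports slower inclusion than anticipated. And any chance difference in baseline disability between the arms passes uncorrected into the one odds ratio the trial will report.

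**Working it through.** **1. The plan's own figure.** Inputs from Sample size {14}: "We assume remission rates of 35% in the IVIg/placebo group, and 65% in the IVIg/IVMP"; two-sided 0.05; 80% power; chi-square. From Trial design {8}: "two treatment arms allocated in a 1:1 ratio".

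Formula (pooled variance under the null, no continuity correction):

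n = [z(0.975)·√(2·p̄·(1−p̄)) + z(0.80)·√(p₁(1−p₁) + p₂(1−p₂))]² / (p₂−p₁)²

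- p̄ = 0.50, so √(2 × 0.25) = 0.7071
- √(0.2275 + 0.2275) = √0.455 = 0.6745
- n = (1.960 × 0.7071 + 0.8416 × 0.6745)² / 0.09 = (1.3859 + 0.5677)² / 0.09 = 42.4, rounded up to 43

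Power = Φ[(0.30·√n − 1.3859) / 0.6745]:

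- n = 43: Φ(0.862) = 80.6%
- n = 48: Φ(1.027) = 84.8%

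Odds ratio: (0.65/0.35) / (0.35/0.65) = 3.45. Attrition: 43/0.90 = 47.8, rounded up to 48. All the stated figures reproduce, so the design meets its target with no covariate.

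**2. What baseline adjustment could add.** The documents give no association between baseline disability and remission, so its strength is varied as an assumption. Simulation, 2,500 trials per setting: marginal remission rates held at 0.35 and 0.65; one standardised baseline score; country split one third to two thirds (the expected 2:1 inclusion ratio); a quarter of patients previously treated (assumed); no effect of the strata (assumed). Power is for the Wald test of treatment, with strata only → with strata plus the baseline score.

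| Odds ratio per SD (assumed) | 43 per arm | 48 per arm | Conditional treatment odds ratio |
|---|---|---|---|
| 1.0 | 79.9% → 79.8% | 84.5% → 84.1% | 3.45 |
| 1.65 | 79.0% → 81.5% | 85.5% → 86.4% | 3.70 |
| 2.2 | 80.4% → 84.8% | 85.3% → 88.2% | 4.09 |
| 2.7 | 80.6% → 86.6% | 83.4% → 88.8% | 4.45 |
| 4.5 | 79.6% → 90.8% | 83.2% → 92.5% | 5.71 |
| 7.4 | 80.0% → 94.1% | 84.4% → 96.9% | 7.63 |

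Monte Carlo error is about 0.8 points per entry (√(0.8 × 0.2/2500)). The gain is about nil at 1.0, 0.9 to 6.0 points for 1.65 to 2.7, and 9.3 to 14.1 points for 4.5 to 7.4.

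A simple approximation agrees. If the within-arm correlation between baseline and remission is ρ, replace n by n/(1−ρ²) in the power formula. At 43 per arm, ρ of 0.2, 0.3, 0.4 and 0.5 gives 82.2%, 84.2%, 87.0% and 90.5%, against 80.6% unadjusted.

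**3. Type I error.** With no treatment effect, 48 per arm and 50% remission in both arms, the baseline-adjusted Wald test rejected in 4.7% to 5.2% of trials. The chi-square test rejected in 4.7% to 5.1%.

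**4. Chance imbalance.** The standardised mean difference in a baseline score has SD √(2/n): 0.216 at 43 per arm and 0.204 at 48. The probability of a difference above 0.2 SD is 35% and 33%, and above 0.3 SD it is 16% and 14%.

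**The case against.** The strongest reply is that nothing is broken. The test named first, and the one powered, is the chi-square. It reaches its target and holds its size, and adjusting for the stratification factors alone is a recognised choice. That stands. A reader might infer that the trial is underpowered or its estimate biased; neither follows. Step 1 shows the target is met, and under randomisation chance imbalance is not bias on average. It affects the particular estimate obtained and its precision.

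Second, the logistic model is an additional analysis, so extra covariates in it leave the chi-square test's power unchanged. This is correct, and the remedy has to say which analysis is primary. The estimate is affected either way, because that model supplies the only named effect size.

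Third, a reader might conclude that mildly disabled patients cannot reach remission. The documents do not support that. Improvement on either scale is enough, the article says the trial is aimed at patients with active disease, and no figure shows how many start near the end of a scale. Room to improve also concerns only the week-18 component. How baseline disability relates to staying stable without treatment to week 52 is not stated, so even the direction of the net association is unknown.

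Fourth, the contrast with the secondary outcomes is limited. Baseline adjustment there applies to continuous scores, in an analysis additional to t tests, and the binary improvement outcome is also tested by unadjusted chi-square. The contrast shows that the plan uses baseline adjustment for these scales. It is not a contradiction.

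Finally, covariate choice is often left to an analysis plan, which is not shown here. But the article does not leave it open: it lists the covariates.

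**Conclusion.** The point holds as one of efficiency. The remission model is specified without a baseline measure that is already collected and that enters the definition of the outcome. The planned analysis is valid and meets its stated 80% power.

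The size rests on an association the documents do not report: essentially no gain or loss if baseline disability is not prognostic, about 1 to 6 points of power for a modest association, and 9 or more only for a strong one. Gains of that last order are possible but should not be expected on the evidence given. The figures assume one normally distributed score, strata without prognostic effect, and the planning rates of 35% and 65%. Separately, there is about a one-in-three chance that the arms differ by more than 0.2 SD on a given baseline score, and the present model would not correct for it. A change is worth making because it costs almost nothing if baseline turns out not to matter.

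**What to change.** Before unblinding, amend Statistical methods, Primary outcome, as follows:

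1. Add the baseline I-RODS logit score, the baseline INCAT-DS, or both, to the logistic model with country and previous treatment. One score suffices if parsimony is preferred.
2. Name this adjusted model as the primary analysis and keep the chi-square test as supportive. Without this step the power of the main test does not change.
3. Report the standardised (marginal) difference in remission rates beside the odds ratio, and label the odds ratio as conditional. At an assumed odds ratio per SD of 2.7, for example, the planning value of 3.45 corresponds to a conditional 4.45, so the two must not be compared directly. The marginal difference stays comparable with the planned 30 points.

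Cost: wording only, with no new data or visits. One or two parameters are added. With 48 per arm at the planning rates, about 0.35 × 48 + 0.65 × 48 = 48 remissions and 48 non-remissions are expected, for a model with four or five terms besides the intercept. The remaining downside is that a conditional odds ratio needs the marginal difference next to it to be read against the design.
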